**Fig. 4 Fig4:**
[figure not shown]
Overview of study visits. FU, follow-up

**Table 1 Tab1:** Schedule of activities

Activities	Screening	Baseline	Day of Surgery	Early PostOP	FU d3	FU d14	FU d30	FU every 12w
I/E criteria	✔	-	-	-	-	-	-	-
Demographics, medical history	✔	-	-	-	-	-	-	-
Written informed consent	-	✔	-	-	-	-	-	-
Vital signs (heart frequency, blood pressure, body temperature), weight	-	✔	-	✔	✔	✔	✔	✔
Physical examination	-	✔	-	✔	✔	✔	✔	✔
Neurological examination (NANO scale)	-	✔	-	✔	✔	✔	✔	✔
Orthoptic examination	-	✔	-	-	-	✔	-	-
Seizure status (ILAE)	-	✔	✔	✔	✔	✔	✔	✔
Current medication (including steroids)	-	✔	✔	✔	✔	✔	✔	✔
ASA score	-	✔	-	-	-	-	-	-
KPS	-	✔	-	✔	✔	✔	✔	✔
MMSE	-	✔	-	-	-	✔	✔	✔
Modified Rankin Scale (mRS)	-	✔	-	✔	✔	✔	✔	✔
Neurocognitive testing (VLMT, Boston Naming test, EpiTrack ®)	-	✔	-	-	-	-	✔	✔
QoL questionnaire (EORTC-QLQ-C30 and BN20)	-	✔	-	-	-	✔	✔	✔ ^c^
Complete blood count	-	✔	-	✔	✔	-	-	-
Coagulation analysis (including preoperative tests as specified in 2.7)	-	✔	-	✔	-	-	-	-
Serum chemistry	-	✔	-	✔	✔	-	-	-
Pregnancy test ^b^	-	✔	-	-	-	-	-	-
Gadolinium-enhanced MRI	-	✔	-	-	✔	-	-	✔
EEG	-	✔	-	-	-	-	✔	-
Adverse events (CTCAE)	-	-	✔	✔	✔	✔	✔	-
Randomization	-	-	✔	-	-	-	-	-
Surgery-related data (IOM, duration, blood loss, intraoperative seizures etc.)	-	-	✔	-	-	-	-	-
Survival status ^a^	-	-	-	✔	✔	✔	✔	✔
Periprocedural adverse events (PSIs, CSCs)	-	-	-	✔	✔	✔	✔	✔ ^d^
Length of mechanical ventilation	-	-	-	✔	✔	✔	-	-
Histopathological results	-	-	-	-	-	-	✔	-
Length of hospital stay	-	-	-	-	-	✔	✔	✔
Radiotherapy (day of start, number of days, total Gy)	-	-	-	-	-	✔	✔	✔
Tumor-directed medical therapy (drug, dose, schedule)	-	-	-	-	-	✔	✔	✔
Other tumor-directed treatment (e.g. TTFs)	-	-	-	-	-	✔	✔	✔
Assessment of progression (RANO 2.0 criteria)	-	-	-	-	-	-	-	✔

*AS*, American society of anesthesiologists, *CSCs* cranial-surgery-related complications, *CTCAE* common terminology criteria for adverse events, *d* day, *EEG* electroencephalography, *EORTC* European organization for research and treatment of cancer, *FU* follow-up, *Gy* Gray, *I/E* inclusion/exclusion, *ILAE* International League Against Epilepsy, *KPS* Karnofsky performance scale, *MMSE* mini mental state examination, *PSIs* patient safety indicators, *QLQ* quality of life questionnaire, *RANO* response assessment in neuro-oncology, *VLMT* Verbaler Lern- und Merkfähigkeitstest

^a^ until end of the trial, i.e. 3 years after randomization of the last patient or until death

^b^ for women with childbearing potential

^c^ after day 90 visit (first 12 week FU): every 24 weeks

^d^ only until day 90

Postoperative visits are scheduled as follows: Visit 4 will occur on Day 1 (early postoperative), Visit 5 on Day 3 (postoperative), Visit 6 on Day 14, Visit 7 on Day 30, and Visit 8 on Day 90. Subsequent follow-up visits will be conducted every 12 weeks (± 5 days) until death. AEs will be assessed according to CTCAE5, starting from Visit 2 and continuing through Visit 7. Particular attention will be given to postoperative complications, which will be recorded from Visit 4 through Visit 8, with potential late-onset complications assessed during Visit 8.

Timing deviations from the defined schedule are considered protocol violations under certain conditions. For Visit 6, a deviation of more than 2 days is regarded as a violation, while for Visit 7 and all subsequent visits, deviations of more than 5 days are considered violations. No deviations are permitted for Visits 2 through 5.

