#### Quality of life

The EORTC QoL questionnaire modules QLQ-C30 and BN20 will be used to evaluate the QoL of patients [45–47]. These well-validated and internationally recognized tools assess QoL across 26 domains. Based on prior studies [40, 48, 49], specific domains of particular relevance for brain tumor patients will be emphasized, including global health status, physical functioning, social functioning, cognitive functioning, communication deficit, and motor dysfunction. The questionnaire is designed to be completed within approximately 10 min in both the pretreatment phase and during ongoing treatment.

The questionnaire's validity has been demonstrated across various cancer populations and disease stages, including their respective treatments. Test–retest reliability, assessed within a four-day interval, has shown good to excellent consistency for all functional scales, with Pearson’s r values ranging from 0.72 to 0.91 [45–47, 49–51].

For this trial, patients will complete the questionnaires using tablets as electronic patient-reported outcomes (ePRO) devices. Study staff will assist patients in handling the ePRO instruments and ensure the completeness of responses before releasing the data for transfer. QoL assessments will be conducted at the baseline visit, on follow-up days 14 and 30, and at each 12-week visit.

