#### Neurocognitive functioning

Neurocognitive function will be assessed using a test battery specifically designed to evaluate temporo-lateral, temporo-mesial, and frontal lobe functions, including memory, language, and executive functions. All tests have been validated for use in monitoring and outcome evaluation in temporal lobe epilepsy surgery [20, 21, 52, 53]. Cognitive functions across all domains will be quantitatively assessed preoperatively and postoperatively at Visit 7 (Day 30), Visit 8 (Day 90), and every 24 weeks until the conclusion of the trial. These assessments will focus on both group-level and individual-level changes over time.

Neurocognitive test battery consists of the VLMT (duration: 30 min including 20 min break between learning and retention) for verbal memory [28, 29], Boston Naming Test (duration: max. 5 min) for naming [30] and the EpiTrack® (duration: max. 15 min) for executive functions [31].

All chosen tests are standard for monitoring epilepsy surgery and temporal lobe surgery in particular [21]. The VLMT is a verbal learning and memory test that follows a list-learning paradigm with a 15-word list (A) to be learned over five learning trials with immediate recall, followed by learning a distractor list (B) once. This is followed by free recall of list A after distraction by learning and recalling list B and again after a delay. Finally, there is a recognition trial that requires identifying list A words from a list containing list A and B words, as well as new distractor words that are phonemically or semantically related to list A and B words. The test has proven its sensitivity to temporal lobe pathology and surgery in several studies [54–60].

The EpiTrack® is a short screening test for executive functions comprising subtests which assess psychomotor speed, mental flexibility, response inhibition, fluency, working memory, and anticipation. The EpiTrack® and its subtests are sensitive to frontal lobe functioning [61, 62] and to CNS drug effects and have been used to monitor epilepsy surgery [63, 64]. The Boston Naming test assesses naming and word finding in the language domain and is a standard procedure to monitor language functions in epilepsy surgery [65, 66].

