## Statistics and analysis

### Sample size calculation

The sample size calculation is based on the primary endpoints of OS and QoL, with equal allocation of subjects to the two treatment groups. Assuming a two-sided alpha level of 5%, median OS times of 17 months in the control group and 27.5 months in the experimental group, a 3-year accrual period, and a 3-year follow-up period (resulting in a total trial duration of 72 months), a total of 170 subjects with a confirmed diagnosis of glioblastoma will provide 80% power to test the null hypothesis of equal OS between the two groups (two-sided log-rank test). The assumed survival benefit of a 10-month improvement with ATL over GTR is based on existing data from retrospective glioblastoma surgery studies involving ATL [16, 25] as well as analyses of EORTC datasets that are not specific to temporal tumor localization [9].

It is anticipated that approximately 4.5% of randomized patients will not have glioblastoma CNS WHO grade 4 but rather a different subtype of diffuse high-grade glioma, as determined by the final integrated histopathological and molecular diagnosis according to the 2021 WHO classification [55]. If the final diagnosis does not confirm glioblastoma IDH wildtype (CNS WHO grade 4), these patients will remain in the trial for safety follow-up but will be replaced in their respective groups and excluded from the mITT population. This replacement strategy will result in a maximum of 178 randomized patients. All randomized patients, regardless of diagnosis, will undergo regular follow-up as outlined in the trial protocol for safety monitoring.

The two primary endpoints will be analyzed in a hierarchical order, with QoL being tested for non-inferiority in the experimental group compared to the control group if the null hypothesis for OS is rejected. QoL measurements will be conducted quarterly, and a prior study demonstrated an approximately linear time dependence of the QoL (= global health) score on time [49].

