A simulation was performed to assess the non-inferiority of the slope of QoL scores over time in the two treatment groups, with a non-inferiority margin of 0.4 score points (using the quarter as the time unit). The simulation incorporated survival status based on the previously stated assumptions and assumed a compound symmetry for the correlation structure of QoL scores across time points, with a correlation coefficient of 0.7. The results indicate that a total of 170 evaluable subjects in the mITT population will provide approximately 80% power to test for non-inferiority of QoL (linear mixed-effects model with QoL score as dependent variable, random patient intercept, and treatment group + time as independent variables, 95% confidence interval of the interaction between time and treatment, 1000 Monte Carlo replications, mean power 83%, Monte Carlo error 1.2%).

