### Primary outcome

The statistical analysis will be conducted at the Study Center Bonn (SZB) of the University of Bonn Medical Center under the direction of [name]. [name]. The primary, confirmatory analysis will compare OS between the treatment groups using a two-sided log-rank test at a significance level of 5%. This analysis will be performed on the mITT population. The log-rank test will be stratified by age group (< 50 years or ≥ 50 years) and pre-operative KPS class (70–80% vs. 90–100%). Surviving patients and those lost to follow-up will be censored at the respective time points. OS will be summarized using Kaplan–Meier curves, with median survival estimates and corresponding 95% confidence intervals reported.

A sensitivity analysis for OS will be conducted using a Cox proportional hazards model with treatment group and MGMT promoter methylation status (hypermethylated vs. unmethylated) as independent variables. If the MGMT promoter methylation status is not available, missing data for these patients will be imputed. In another sensitivity analysis for OS, a Cox proportional hazards model with treatment group and center recruitment volume (high vs. low) will be fitted. Additionally, potential prognostic factors, including age, preoperative KPS, MGMT promoter methylation status (hypermethylated vs. unmethylated), and center recruitment volume (high vs. low), will be analyzed using a multivariate Cox proportional hazard model for OS.

If OS of ATL significantly differs from that of GTR, the patient-reported QoL domain "global health status" from the EORTC QLQ-C30 questionnaire will be analyzed as a co-primary endpoint. Changes from baseline in the experimental arm (ATL) will be compared to the standard arm (GTR) to assess non-inferiority, using a non-inferiority margin of 1.6 score points per year. This evaluation will be performed on the mITT population and using a linear mixed-effects model (QoL score as dependent variable, random patient intercept, treatment group + time as independent variables, estimating a 95% confidence interval of the interaction between time and treatment).

Overall superiority of ATL will require significantly prolonged OS alongside non-inferiority in the development of global health status over time. Due to the hierarchical testing approach, no adjustment of the type I error rate is necessary.

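### The co-primary quality-of-life questionnaire is 24-weekly after day 90 in Table 1, but 12-weekly in the assessment text and quarterly in the sample size section

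*Protocol article*

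**What the plan says.** Four places in the protocol article bear on how often patients complete the QLQ-C30 and BN20.

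- **Table 1, QoL row.** Ticks stand at baseline, day 14, day 30 and in the 12-weekly follow-up column. The last tick carries footnote c: "after day 90 visit (first 12 week FU): every 24 weeks".
- **Methods of assessment, Quality of life.** "QoL assessments will be conducted at the baseline visit, on follow-up days 14 and 30, and at each 12-week visit".
- **Sample size calculation.** "QoL measurements will be conducted quarterly". The simulation then tests the slope "with a non-inferiority margin of 0.4 score points (using the quarter as the time unit") and reports "mean power 83%, Monte Carlo error 1.2"%.
- **Methods of assessment, Neurocognitive functioning.** This battery is given at day 30, then "Visit 8 (Day 90), and every 24 weeks until the conclusion of the trial". Its row in Table 1 has no footnote, so the table reads as every 12 weeks.

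The opening of Methods of assessment says that data are documented in the eCRF as Table 1 sets out. The Primary outcome section tests the time-by-treatment interaction in a random-intercept model, "using a non-inferiority margin of 1.6 score points per year".

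**The concern.** The QoL schedules cannot all be followed. All of them are current text, and the article states each one, so this is not detail left to a fuller document.

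The endpoint concerned is co-primary: superiority of ATL needs longer OS and a QoL slope that is not inferior. The precision of a slope depends directly on how many assessments are made and when. If eCRF and ePRO are set up from Table 1, later questionnaires are thinned relative to the text and, on its natural reading, to the power simulation. If sites work from different places in the protocol, the data become uneven. A questionnaire not given at a visit cannot be recovered.

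The per-protocol set is affected too. Missed evaluations count as protocol violations, and the set requires endpoint examinations at predefined times. With two schedules it is undefined whether a missing 12-week questionnaire is a violation.

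**Working it through.** **Inputs from the article.** 170 evaluable patients (85 per arm); median OS 17 and 27.5 months; 36 months of accrual plus 36 of follow-up; compound symmetry with correlation 0.7; margin 0.4 points per quarter; 95% confidence interval; stated power 83% from 1000 replications.

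**Assumed.** Exponential survival, uniform accrual, true slope difference zero, complete questionnaires until death or end of trial. The score SD is not stated.

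**1. The plan's own figures.**
- Margins: 4 × 0.4 = 1.6 points per year, so the two statements agree.
- Monte Carlo error: √(0.83 × 0.17 / 1000) = 0.012, as stated.
- OS: HR = 17/27.5 = 0.618; 136 events needed (Schoenfeld); 137.2 expected among 170; power 80.4%. The survival set-up reproduces the stated 80%.
- QoL power of 83%: not reproducible from stated inputs alone. With quarterly visits it is 97% at SD 15, 82.5% at SD 20 and 64% at SD 25. An SD of about 20 returns the stated figure.

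**2. Number of questionnaires.** Expected totals under the survival assumptions:

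| Schedule | Questionnaires |
|---|---|
| Text: baseline, days 14 and 30, then 12-weekly | about 1970 |
| Quarterly only | about 1524 |
| Table 1: baseline, days 14, 30 and 90, then 24-weekly | about 1277 |
| Table 1 without days 14 and 30 | about 944 |

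Table 1 retains 1277/1970 = 65% of the text schedule and 1277/1524 = 84% of a quarterly one.

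**3. Power under Table 1, calibrated to 83%.** With V = SD² × [0.3 I + 0.7 J] for each patient, the slope variance in an arm is the slope element of (Σ XᵀV⁻¹X)⁻¹. The two arms add. Power = Φ(0.4/SE − 1.96). Setting this to 0.83 gives 0.4/SE = 1.96 + 0.954 = 2.914. The SD then cancels, and only the ratio of standard errors between schedules matters:

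Power under Table 1 = Φ(2.914/ratio − 1.96)

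- Simulated quarterly, days 14 and 30 added in the trial: ratio 1.085, Φ(0.726) = 77%.
- Simulated quarterly, days 14 and 30 not in the model: ratio 1.242, Φ(0.386) = 65%.
- Simulated on the full text schedule: ratio about 1.25, Φ(0.371) = 64–65%.

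**4. Direct check at SD 20.** Quarterly 81–83%; text schedule 91%; Table 1 75–76% with days 14 and 30, and 63–67% without them. Together with step 3 this gives roughly 63–77%.

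**5. Sensitivity.** Correlations from 0.5 to 0.8 leave the calibrated result unchanged (65–77%). A one-sided 5% test gives 67–77%. If QoL collection stopped at 36 months per patient, it would be 57–70%.

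**The case against.** The strongest reply is that the power loss is conditional. The article states no SD, and the simulated visit days are only inferred from the word quarterly and the time unit. On the Table 1 schedule with days 14 and 30, power is about 94% at SD 15, 83% at SD 18, 74–76% at SD 20 and 55% at SD 25. An SD of 18 with Table 1's visits would therefore also return the stated 83%. This stands. A reader might infer that a trial run to Table 1 cannot reach its stated power, or that the true figure is 76%. The documents support neither.

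The comparison of 83% with 77% also mixes grids, since days 14 and 30 are absent from the first and present in the second. Hence the range.

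A reader might say that QoL would be measured half as often as planned. That is true only after day 90, because the assessments up to day 90 are common to the text and Table 1.

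The misplaced footnote is an inference. An intended 24-weekly schedule for both instruments, with the footnote omitted from one row, fits the neurocognitive text and Table 1's QoL row equally well.

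Multiplying the OS and QoL powers into a joint success probability is a separate matter. It would assume independence, although the QoL simulation incorporates survival.

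Finally, the full protocol and the eCRF set-up are not shown, so what sites actually do is unknown. None of this removes the contradiction.

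**Conclusion.** The contradiction is certain and concerns a co-primary endpoint. Thinning later visits lowers the precision of the slope comparison relative to the 12-weekly text schedule; that direction does not depend on the SD.

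The size is conditional. If the 83% was simulated on quarterly or 12-weekly visits, which is what the sample size section suggests, Table 1 gives roughly 63–77%, below both the 83% and the nominal 80%. The loss is about 6 points if the simulation was quarterly only and days 14 and 30 enter the trial's model, and about 18 to 20 points otherwise. The figures rest on calibration to the stated 83%, full completion until death or end of trial, and no true difference in slope.

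**What to change.** Reconcile Table 1 with the Quality of life, Neurocognitive functioning and Sample size sections, so that each instrument has one schedule.

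- **If QoL is meant at every 12-week visit:** remove footnote c from the QoL row, and place it on the neurocognitive row if the text there is what is meant. Cost: one table correction, a site notice, and a questionnaire of roughly 10 minutes at visits already scheduled.
- **If 24-weekly QoL is intended:** amend the Quality of life and Sample size sections, rerun the simulation on the actual visit days with the sponsor's own SD, and restate whatever power results. The range above is no substitute for that rerun. Cost: a text amendment and one simulation.

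In both cases, state the SD and the visit grid behind the power figure, and check that the eCRF and ePRO visit set-up follows the reconciled schedule.

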### Methods of assessment

This section provides an overview and explanations of the examinations and procedures to be conducted in this trial. All data will be documented in the eCRF for indicated visits and follow-up examinations as outlined in the schedule of activities (Table 1).

#### Overall survival and progression-free survival

OS is defined as the time from the day of randomization/day of surgery to the respective patient’s death. Progression is defined as the first documented evidence of progressive disease according to the RANO 2.0 criteria [27]. PFS is measured from randomization at the day of surgery until progression or death.

#### Quality of life

The EORTC QoL questionnaire modules QLQ-C30 and BN20 will be used to evaluate the QoL of patients [45–47]. These well-validated and internationally recognized tools assess QoL across 26 domains. Based on prior studies [40, 48, 49], specific domains of particular relevance for brain tumor patients will be emphasized, including global health status, physical functioning, social functioning, cognitive functioning, communication deficit, and motor dysfunction. The questionnaire is designed to be completed within approximately 10 min in both the pretreatment phase and during ongoing treatment.

The questionnaire's validity has been demonstrated across various cancer populations and disease stages, including their respective treatments. Test–retest reliability, assessed within a four-day interval, has shown good to excellent consistency for all functional scales, with Pearson’s r values ranging from 0.72 to 0.91 [45–47, 49–51].

For this trial, patients will complete the questionnaires using tablets as electronic patient-reported outcomes (ePRO) devices. Study staff will assist patients in handling the ePRO instruments and ensure the completeness of responses before releasing the data for transfer. QoL assessments will be conducted at the baseline visit, on follow-up days 14 and 30, and at each 12-week visit.

#### Neurocognitive functioning

Neurocognitive function will be assessed using a test battery specifically designed to evaluate temporo-lateral, temporo-mesial, and frontal lobe functions, including memory, language, and executive functions. All tests have been validated for use in monitoring and outcome evaluation in temporal lobe epilepsy surgery [20, 21, 52, 53]. Cognitive functions across all domains will be quantitatively assessed preoperatively and postoperatively at Visit 7 (Day 30), Visit 8 (Day 90), and every 24 weeks until the conclusion of the trial. These assessments will focus on both group-level and individual-level changes over time.

Neurocognitive test battery consists of the VLMT (duration: 30 min including 20 min break between learning and retention) for verbal memory [28, 29], Boston Naming Test (duration: max. 5 min) for naming [30] and the EpiTrack® (duration: max. 15 min) for executive functions [31].

All chosen tests are standard for monitoring epilepsy surgery and temporal lobe surgery in particular [21]. The VLMT is a verbal learning and memory test that follows a list-learning paradigm with a 15-word list (A) to be learned over five learning trials with immediate recall, followed by learning a distractor list (B) once. This is followed by free recall of list A after distraction by learning and recalling list B and again after a delay. Finally, there is a recognition trial that requires identifying list A words from a list containing list A and B words, as well as new distractor words that are phonemically or semantically related to list A and B words. The test has proven its sensitivity to temporal lobe pathology and surgery in several studies [54–60].

The EpiTrack® is a short screening test for executive functions comprising subtests which assess psychomotor speed, mental flexibility, response inhibition, fluency, working memory, and anticipation. The EpiTrack® and its subtests are sensitive to frontal lobe functioning [61, 62] and to CNS drug effects and have been used to monitor epilepsy surgery [63, 64]. The Boston Naming test assesses naming and word finding in the language domain and is a standard procedure to monitor language functions in epilepsy surgery [65, 66].

The Boston Naming Test [30] and EpiTrack® [31] will be performed during the 20-min break of the VLMT [28, 29]. Consequently, the entire neurocognitive test battery will take no more than 30 min, ensuring it is well-tolerated by brain tumor patients. This test battery can be conducted by a study nurse and does not require the presence of a neuropsychologist.

The mini mental state examination (MMSE), a general test for neurocognitive functioning with a maximum score of 30 points [67], assesses various cognitive domains, including orientation, concentration, delayed recall, visual construction, and aphasic problems. The MMSE [67] will be performed at baseline, on follow-up days 14 and 30, and at each 12-week visit.

